### 2.6. Data Collection

The planning of the study will include an enrolment period lasting 12 months, starting from the involvement of the first patient after 15 June 2024. The study follow-up will last six months. After this period, all the patients will be referred to current clinical practice. Nurses will record digital data from patients’ self-reports and nurses’ interviews and observations in a specific database.

Patients in the control arm will be treated according to current clinical practice, mainly with the support of oncologists. The paper questionnaires that patients and nurses will complete during the study will be recorded by nurses in a specific database.

Data from patients enrolled in the intervention group will be collected via electronic questionnaires, similar to those of nurses. Data collection for the outcomes described in Table 1 will be assessed at baseline (T0), after 30 (T1), 90 (T2) and 180 days (T3). In addition, patients will transmit data daily relating to the monitoring of vital parameters and AEs described in the section on the primary and secondary objectives.

### 2.7. Data Analysis

Intention-to-treat analysis will be applied in case of abandonment of a patient from one arm or the other. The rigor observed in the study will be aimed at acquiring detailed and exhaustive information. However, missing data due to incomplete or partial registration by the patient will be treated with appropriate statistical techniques. Descriptive statistics will explore the continuous variables through the means and standard deviations (±SD), while the categorical variables will explore the absolute frequencies and percentage values. The Kolmogorov–Smirnov normality test will be used for all the continuous variables. The Chi-square or Fisher’s exact test will assess the potential associations between categorical variables. The differences for continuous variables will be explored using the nonparametric Mann–Whitney U test or Student’s *t* test, depending on the nature of the distributions of the variables examined. All the statistical analyses will be performed using Statistical Package for the Social Sciences (SPSS) Software 29.0 (IBM SPSS Statistics for Windows, Version 29.0. Armonk, NY, USA: IBM Corp.) for Windows. A *p*-value < 0.05 will be considered statistically significant.

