### 2.2. Study Setting and Sampling

The RCT will be performed in a national cancer centre starting on 1 April 2024. A nursing team will lead the project in collaboration with medical oncologists. The sample size calculation was performed on the primary outcome, the SCNs scale [18,19] measured one month after treatment, considering possible losses to follow-up (drop-out rate). The study by Ebrahimabadi [18] allowed the researchers to hypothesise the following:A mean score and its relative standard deviation (SD) in the intervention group equal to 81.53 (±13.2),A mean score and its relative SD in the control group equal to 103.5 (±21.96), with a statistical power of 90% and a significance level α = 0.05, while a two-tailed Student’s *t*-test estimated an overall size of 32 patients, 16 for each group. Given the mean score reported in the hypothesis system, we obtain an effect size equal to 1.21. Considering a drop-out rate of 20%, we will enrol a total sample of 40 patients. The software NCSS PASS v.11.0 was used to assess the minimum size. Evaluation of the statistical tests will be carried out by an expert statistician.

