
After nurses have obtained the informed consent, 40 patients with melanoma and lung cancer (20 in each group) will be randomised into the IA (telenursing intervention added to clinical practice) or the CA (clinical practice). To allow for comparison, at baseline (T0) before the randomisation, patients from both groups will complete the tools shown in Table 1 in paper format. Additionally, patients involved in the study will use the study tools according to the timelines described in Table 1 at T1 (30 days), T2 (90 days), and T3 (180 days). Regarding the practice procedures, monthly telenursing interventions will be provided every 30 days, on dates agreed in advance with patients. However, patients will be able to communicate with the nursing staff via short messages or by telephone at any time of the day, between 8 a.m. and 2 p.m. An unplanned nursing intervention can be useful in case of patient doubts or problems related to therapeutic adherence (dosage errors, forgotten or double doses, etc.), onset of new side effects, sudden alterations in vital signs, etc. In addition, in view of the daily questionnaire filled out by patients (Table 1), nursing staff will implement additional interventions as needed, remotely or in person.

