### 3.1. Strengths and Limitations of the Work

To the best of the authors’ knowledge, this is the first RCT to assess the impact of telenursing interventions on the clinical pathway of patients with melanoma and lung cancer on TT. In particular, it could be helpful to assess the effects of a broader nursing contribution on the SCNs [18,19] at one month (primary outcome), the main AEs, therapeutic adherence [24,25], QoL [20,21], system usability and satisfaction [22,23], performance status [26] and PROs at one, three and six months (secondary outcomes).

The authors are aware of the limitations of the study. First, the small sample size and the two cancer types enrolled (lung cancer and melanoma) should be considered. Furthermore, the lack of stratification by age and pathology may not allow the authors to capture differences or risk classes to consider through inference on a larger sample. The enrolment of patients in the exclusive TT does not allow for the inclusion of patients who probably could benefit from the interventions in the study. However, to reduce the weight of the limitations of the present study protocol, the authors trust in the methodological rigour of the study design.

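### The stated test for the primary outcome makes no use of the pre-randomisation supportive care needs score; a prespecified ANCOVA would gain precision at almost no cost

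*Protocol article*

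**What the plan says.** The primary outcome is the SCN score one month after the start of treatment, T1 (Sections 1.2 and 2.2). Table 1 lists the scale at T0, T1, T2 and T3. Section 2.4 states that "at baseline (T0) before the randomisation, patients from both groups will complete the tools shown in Table 1 in paper format". The baseline score is therefore pre-treatment and collected in the same format from both arms.

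Section 2.7 gives one sentence on comparing continuous variables: "The differences for continuous variables will be explored using the nonparametric" Mann–Whitney U test or Student's t test, according to the distribution. Section 2.2 sizes the trial on a two-tailed t-test of the one-month means, which "estimated an overall size of 32 patients, 16 for each group". No ANCOVA, change score, mixed model or other use of the baseline score is described.

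Allocation is 1:1 with no stratification factor named (Section 2.5). Section 3.1 lists as a limitation that "the lack of stratification by age and pathology may not allow the authors to capture differences or risk classes".

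**The concern.** A patient's SCN score before treatment will usually predict the score a month later. A two-sample test of the T1 scores leaves that predictable part of the variation in the error term. This has two consequences.

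- The confidence interval is wider than the collected data require whenever the correlation is more than weak. This matters most if the true effect is smaller than the very large one assumed.
- In a small trial without stratification by age or pathology, the arms can start some points apart by chance. The unadjusted estimate carries part of that gap into T1, and readers of this one trial cannot separate it from the treatment effect.

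The measurement that would address both is already scheduled.

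**Working it through.** **Inputs from Section 2.2.** Means 81.53 (intervention) and 103.5 (control); SDs 13.2 and 21.96; 90% power; two-sided α = 0.05; 20% drop-out. **Assumed, because the document does not give them:** T0–T1 correlation r = 0.3 to 0.7; baseline SD about equal to the pooled one-month SD.

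**1. The plan's own figure.**
- Difference = 103.5 − 81.53 = 21.97.
- Pooled SD = √((13.2² + 21.96²)/2) = 18.12.
- Effect size = 21.97/18.12 = 1.21, as stated.
- Noncentral-t power is 89.3% at 15 per arm and 91.3% at 16 per arm, so 16 per arm (32 in all).
- 32/(1 − 0.20) = 40.

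The stated sample size reproduces.

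**2. Precision of the unadjusted test.** SE = 18.12 × √(2/16) = 6.41. With 30 degrees of freedom the 95% CI half-width is 13.1 points.

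**3. Large-sample effect of adjustment.** The variance is multiplied by 1 − r², and one further degree of freedom is spent.

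| r | 1 − r² | Half-width (points) | Gain, 1/(1 − r²) − 1 |
|---|---|---|---|
| 0.3 | 0.91 | 12.5 | 10% |
| 0.5 | 0.75 | 11.4 | 33% |
| 0.7 | 0.51 | 9.4 | 96% |

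This formula is too favourable at 16 per arm. It ignores the cost of estimating the slope and the unequal SDs.

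**4. The model at the actual size.** Simulation of ANCOVA with baseline SCN as the only covariate, 16 per arm, normal scores with SDs 13.2 and 21.96:

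| r | Efficiency gain | Half-width, model-based SE | Half-width, HC3 SE |
|---|---|---|---|
| 0.3 | about 6% | about 12.6 | about 13.3 |
| 0.5 | about 26% | about 11.5 | about 12.1 |
| 0.7 | about 79% | about 9.7 | about 10.2 |

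The unadjusted half-width is about 13. With HC3 the interval at r = 0.3 is no narrower than that.

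**5. If the true effect is half that planned.** At 16 per arm the unadjusted power is 38%. The formula in step 3 gives 41%, 48% or 64% for r = 0.3, 0.5 or 0.7. These are slightly optimistic for the reason given there.

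**6. Chance baseline gap.** Twenty patients per arm are randomised. The SD of the baseline mean difference is 18.12 × √(2/20) = 5.73 points. P(gap > 5 points) = 2 × (1 − Φ(5/5.73)) ≈ 38%. With equal SDs at T0 and T1, a 5-point gap moves the unadjusted T1 difference by about r × 5 = 1.5, 2.5 or 3.5 points, against a planned difference of 21.97. A gap above 0.5 SD (about 9 points) has a probability of about 11% and moves it by about 2.7, 4.5 or 6.3 points.

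**The case against.** The strongest reply is that the stated method is sound. Under 1:1 randomisation the unadjusted test keeps its type I error and is unbiased on average, and its standard error already allows for chance baseline gaps. It also matches the basis of the sample size. That stands. A reader might infer that the primary analysis is biased or the trial underpowered, but the document supports neither: 16 per arm gives 91.3% power unadjusted if the assumed effect is true.

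Second, the gain rests on an unknown correlation, which may be low. T0 falls at the first prescription and T1 after a month of treatment, when the Introduction says adverse events weigh heavily. The intervention arm also moves from paper to electronic forms. This stands too, which is why 0.3 is shown and the gain there is small or absent.

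Third, the article is condensed and a fuller analysis plan may name covariates. It is also not explicit on whether the T1 score or the change is tested, although the means in Section 2.2 point to the T1 score. It would therefore go too far to say that the investigators will ignore the baseline. But Section 2.7 does state the tests and Section 2.2 agrees with them, so the comment is on a stated choice and not on silence.

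A reader might also infer that tumour type must be adjusted for or the list stratified by it. The document does not say that the two cancers differ in symptom burden, and it gives no expected split between them. Section 1 justifies including both by incidence and common therapeutic approaches. The case rests on baseline SCN alone.

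**Conclusion.** The point holds as an inexpensive improvement, not as an error. The stated comparison is valid and adequately sized for its assumed effect, but it uses less information than the trial collects. For r from 0.3 to 0.7 and 16 evaluable patients per arm, ANCOVA on baseline SCN is worth about 6% to 79% in efficiency. With a model-based standard error the half-width is about 0.4 to 3.3 points narrower than 13. With HC3 the benefit disappears at the low end. The 38% chance of a baseline gap above 5 points depends on an assumed baseline SD of about 18.1. Such a gap would move the T1 difference by only a few points, so adjustment refines the estimate and would rarely reverse a 22-point effect. It matters more if the true effect is well below that.

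**What to change.** Before any outcome data are examined, amend Section 2.7 as follows.

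- Name ANCOVA of the T1 SCN score on arm and baseline SCN score as the single primary analysis.
- Report the adjusted mean difference with its 95% CI, and state in advance which standard error is used.
- Keep the unadjusted test as a sensitivity analysis.
- Treat SCN at T2 and T3, and the other scales with a T0 value (SF-36, MARS-5I, Karnofsky), in the same way. The System Usability Scale has no T0 value and is not affected.
- Tumour type may be added as a covariate but need not be. It costs a further degree of freedom and repays it only if it is prognostic.

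The cost is one model degree of freedom, a change of wording, and submission of that change to the ethics committee as Section 2.8 requires. No new data are needed, the named software can fit the model, and N stays at 40.

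### The choice between comparing means and comparing ranks for the primary outcome is left to the trial data; naming Welch's t-test in advance would settle it at almost no cost

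*Protocol article*

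**What the plan says.** Protocol article, section 2.7 (Data Analysis): a Kolmogorov-Smirnov "normality test will be used for all the continuous variables". Differences in continuous variables are then examined by Mann-Whitney U or Student's t, "depending on the nature of the distributions of the variables examined", at p < 0.05. The primary outcome, SCN at T1, is not treated separately. The section does not say outright that the Kolmogorov-Smirnov result decides the choice, but that is the natural reading. On any reading the choice depends on the observed data.

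Section 2.2 (Study Setting and Sampling) commits to one test for sizing. It assumes a mean of 81.53 (SD 13.2) under intervention and 103.5 (SD 21.96) under control, "with a statistical power of 90% and a significance level α = 0.05". A two-tailed Student's t-test "estimated an overall size of 32 patients, 16 for each group", raised to 40 for 20% drop-out. Section 2.5 sets 1:1 allocation and states that patients and staff are not blinded.

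**The concern.** Student's t compares means and Mann-Whitney compares rank order. They estimate different quantities and can disagree when the arms differ in spread or shape. The sample size is justified for the first only. In an unblinded trial of 40 patients, the primary effect measure should not wait on the data.

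The second issue is variance. The planning SDs have a variance ratio of about 2.8, and the only parametric test named pools the two variances. Pooling does little harm when arms are equal in size, but it gives the wrong standard error when they are not. Unequal completers are possible here: 20% drop-out is expected, section 2.5 allows exclusion after 15 days of missing data, and missing entries come to light differently in the two arms (electronic forms checked daily against paper forms collected monthly, sections 2.4 and 2.4.1). What is at stake is the accuracy of the primary p-value and confidence interval.

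**Working it through.** **Inputs (section 2.2):** means 81.53 and 103.5; SDs 13.2 and 21.96; two-sided α 0.05; 16 per arm; 20% drop-out.

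**The plan's own figure.** Difference = 103.5 − 81.53 = 21.97. Averaged SD = √[(13.2² + 21.96²)/2] = √[(174.24 + 482.24)/2] = 18.12. Effect size = 21.97/18.12 = 1.21, as stated. Noncentral-t power is 89.3% at 15 per arm and 91.3% at 16, so 16 per arm is right, and 32/0.8 = 40. The sizing reproduces.

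**Variance ratio.** 482.24/174.24 = 2.77 (SD ratio 1.66).

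**Why imbalance matters.** With n₁ intervention and n₂ control completers, Student's t uses SE = √[s²ₚ(1/n₁ + 1/n₂)], with s²ₚ = [(n₁−1)·174.24 + (n₂−1)·482.24]/(n₁+n₂−2). The correct SE is √(174.24/n₁ + 482.24/n₂). At 18/14, s²ₚ = (17·174.24 + 13·482.24)/30 = 307.7. The pooled SE is then √(307.7 × 0.1270) = 6.25, against a correct √(9.68 + 34.45) = 6.64.

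**Error rates.** Simulation of 40,000 trials per row: normal data, equal means, SDs 13.2 and 21.96. The selection rule is Kolmogorov-Smirnov with estimated mean and SD at 5%, then Student's t or Mann-Whitney. Its range covers a gate applied to each arm or to the pooled data. Monte Carlo error is about 0.1 point near 5%. The unequal splits are assumptions, not figures from the plan.

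| Completers (intervention/control) | Pooled SE | Correct SE | Student's t | Selection rule | Welch |
|---|---|---|---|---|---|
| 16/16 | 6.41 | 6.41 | 5.2% | 5.1–5.3% | 5.0% |
| 20/20 | 5.73 | 5.73 | 5.3% | 5.1–5.5% | 5.1% |
| 18/14 | 6.25 | 6.64 | 6.6% | 6.3–6.7% | 5.0% |
| 20/12 | 6.19 | 6.99 | 8.4% | 7.9–8.5% | 5.0% |
| 12/20 | 7.02 | 6.22 | 3.0% | 3.0–3.2% | 4.9% |

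For normal data a shift in means leaves these rates unchanged, so they are also the non-coverage of Student's 95% confidence interval at the planned effect.

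**Equal SDs.** With normal data the rule stays at 4.8–5.3% for every split. With identical gamma (shape 2) arms it is about 5.2–5.5%.

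**Skew with unequal SDs, equal means, equal arms (assumed shape).** For gamma (shape 2) at 16–20 per arm, the rule rejects about 8–9% of the time if the gate is applied to each arm, and about 6.6–7.5% if applied to pooled data. Student's t alone stays near 5.5%. The excess comes from the Mann-Whitney branch, which responds to the difference in distributions although the means are equal.

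**The gate itself.** At 16 per arm it flags gamma (shape 2) skew in one given arm 26% of the time, so in at least one arm 1 − 0.74² = 45%. For two normal arms the corresponding false-alarm rate is 1 − 0.95² = 9.75%.

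**Power at the planned effect, 16 per arm.** Student's t 91.3% and Welch 90.9% (noncentral t); Mann-Whitney 88.6% and the selection rule 90.1–90.9% (simulation).

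**The case against.** The strongest reply is that the SDs of 13.2 and 21.96 belong to the hypothesised effect. If the intervention does nothing, randomised arms share one distribution and equal SDs are the natural assumption; the rule then holds its level for every split tried. This stands as an answer to a type I error claim. It does not cover the confidence interval at the planned effect, where the unequal SDs are exactly what the plan assumes.

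The large departures also need imbalance that the plan does not predict. If eight of 40 patients drop out at random, the chance that all eight come from the control arm (20/12) is C(20,8)/C(40,8) = 0.16%. Exactly 18/14 has probability C(20,2)·C(20,6)/C(40,8) = 9.6%, so the 6.6% figure is the realistic one. Section 2.7 also promises intention-to-treat analysis and treatment of missing data, which could keep the analysed arms near 20/20. That stands too, although no method is named and so balance is not assured.

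A reader might infer that the gate is little better than chance. The figures do not support this: like for like it flags 45% of skewed pairs against about 10% of normal ones. It is weak, not arbitrary.

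Finally, the choice between pooled and Welch variance is often left to an analysis plan, and none is shown. But section 2.7 does not leave the choice of test open for later. It states a data-dependent rule, and that rule does not match the sizing in section 2.2.

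**Conclusion.** The point holds as a cheap improvement. What is certain from the text is that the primary comparison may be of means or of ranks according to the data, while the sample size rests on means and Student's t.

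The numerical consequences are conditional. With equal arms and normal data, or with equal SDs, error is about 5.0–5.5%. If the planned SDs apply and completers are unequal, error or non-coverage is about 6.6% at 18/14, with 8% and 3% at the assumed extremes. If scores are also skewed (gamma, shape 2, assumed), the rule rejects equal means about 8–9% of the time with equal arms and a gate on each arm, through Mann-Whitney.

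A reader might go further and conclude that the 5% error rate is lost, that Student's t is valid only if drop-out is equal, or that the sample size is wrong. The documents support none of these: the level holds under the planned 1:1 design with normal scores, and the sizing reproduces exactly.

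**What to change.** In section 2.7, remove the normality gate for the primary outcome. State that the primary analysis is the difference in mean SCN at T1, tested by Welch's t-test and reported with its 95% confidence interval. Report Mann-Whitney as a sensitivity analysis whatever the distribution looks like. This takes about two sentences.

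The cost is about 0.4 points of power at 16 per arm (90.9% against 91.3%), still above the 90% target, and power is 96.0% at 20 per arm. The 32 evaluable and 40 enrolled patients do not change. Welch is not perfect under strong skew combined with unequal completers: for exponential-shaped scores at 20/12 it rejects 7.1%, but Student's t then rejects 8.7% and Mann-Whitney 14.3%.

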### 1.2. Primary and Secondary Objectives

The objectives of this study will be measured in two compared groups.

Primary objective: To assess the impact of telenursing interventions on the supportive care needs (SCNs) [18,19] in patients with lung cancer and melanoma at the first prescription of TT after one month of treatment (T1). Secondary Objectives: To explore the differences between the AEs reported by healthcare professionals and the patient-reported outcomes and develop a specific nursing reporting system to improve the quality, safety and continuity of cancer care. Further secondary outcomes are shown in Table 1, together with the tools, timing, and users involved in the data collection. Among the secondary outcomes, the SCNs over time (until the end of the study) [18,19], quality of life [20,21], patient satisfaction [22,23], therapeutic adherence [24,25] and performance status [26] will be assessed and compared in both groups. Moreover, the incidence and severity of the following vital signs and adverse events will be compared to highlight the effectiveness of the telenursing intervention with tools based on the Common Terminology Criteria for Adverse Events (CTCAE) [27]: body temperature, blood pressure, heart rate, body weight, pain, stomatitis and mucositis, dysgeusia, nausea and vomiting, diarrhoea, loss of appetite, fatigue, headache, dermatologic reactions, cough and dyspnoea, pain, palmar–plantar erythrodysesthesia, bleeding events, photosensitivity, ophthalmological reactions, sleep, mood and voice disorders.

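### A single unadjusted 0.05 threshold covers 21 symptom and vital-sign comparisons meant to show effectiveness, so an isolated false significant result is likely (up to about 66% in either direction, 41% favouring telenursing)

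*Protocol article*

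**What the plan says.** Section 2.7 (Data Analysis) names the tests for categorical variables (Chi-square or Fisher's exact) and for continuous variables (Student's t or Mann–Whitney). It ends with a general rule that a p-value below "0.05 will be considered statistically significant". The rule is not limited to the primary outcome.

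Section 1.2 (Primary and Secondary Objectives) names one primary outcome, SCN at T1 (one month). Among the secondary objectives it says that "the incidence and severity of the following vital signs and adverse events will be compared to highlight the effectiveness of the telenursing intervention", and a long list follows. Section 2.4 gives the Table 1 measurements in general a similar purpose. Section 1.2 also has SCN over time, quality of life, satisfaction, adherence and performance status compared between the groups. Table 1 schedules follow-up measurement of these at T1, T2 and T3.

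Section 2.2 bases the sample size on SCN at T1 alone, "with a statistical power of 90% and a significance level α = 0.05", and specifies a two-tailed test.

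**The concern.** The threshold in 2.7 and the purpose in 1.2 have to be read together. The first calls any p-value below 0.05 significant. The second says that the symptom and vital-sign comparisons serve to show that the intervention works. A trial of 40 patients, sized for one comparison, would thus run dozens of tests, each allowed to carry the same label as the primary.

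What is at stake is the interpretation of the secondary results. One or two symptoms with p < 0.05 could be reported as significant signs of effectiveness when chance alone would often produce them. The validity of the primary test is not at stake.

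**Working it through.** **The plan's own figure.** Section 2.2 assumes means of 81.53 (SD 13.2) and 103.5 (SD 21.96).
- Pooled SD = √((13.2² + 21.96²)/2) = 18.12.
- Standardised difference = (103.5 − 81.53)/18.12 = 21.97/18.12 = 1.21. This agrees with the protocol: "we obtain an effect size equal to 1.21".
- At two-sided 0.05 and 90% power, the noncentral t solution is 15.3 per arm, hence 16 per arm and 32 in all (power about 91%). Allowing for 20% drop-out, 32/0.8 = 40.

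The sample size reproduces. It covers one test.

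**Counting the tests.** The list in section 1.2 holds 4 physiological measures (temperature, blood pressure, heart rate, weight) and 17 symptoms or reactions. Pain appears twice and is counted once; sleep, mood and voice disorders are counted as three. Total: 21. The other secondary comparisons, with each instrument taken as one score, are SCN at T2 and T3 (2) and SF-36, SUS, MARS-5I and Karnofsky at three visits each (12). That makes at least 14, and 21 + 14 = 35.

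**Chance of at least one false significant result.** Assume no true effect, k independent tests and two-sided testing throughout (2.7 does not state sidedness, so this is taken from 2.2). The chance in either direction is 1 − 0.95^k. The chance in favour of telenursing is 1 − 0.975^k, because half of each test's 5% lies in that direction.

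| Tests | Either direction | Favouring telenursing |
|---|---|---|
| 1 (primary only) | 5% | 2.5% |
| 21 (list in 1.2) | 1 − 0.95^21 = 65.9% | 1 − 0.975^21 = 41.2% |
| 35 (list plus 14) | 1 − 0.95^35 = 83.4% | 1 − 0.975^35 = 58.8% |

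The expected number of false significant results among 21 tests is 21 × 0.05 = 1.05. The chance of a false result favouring telenursing passes one half at ln 0.5/ln 0.975 = 27.4, so at 28 independent tests.

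**Sensitivity to correlation.** The documents give no correlations. The values below are assumptions; the results come from simulation with equally correlated normal test statistics.

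| Assumed correlation | 21 tests, either | 21 tests, favouring | 35 tests, favouring |
|---|---|---|---|
| 0.1 | 64% | 37% | 51% |
| 0.3 | 55% | 29% | 38% |
| 0.5 | 43% | 22% | 27% |

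**Sensitivity to the choice of test.** Suppose the 17 symptoms are analysed as yes/no by Fisher's exact test with 20 patients per arm. At assumed event rates of 5% to 50%, the actual size of each test is only 0.2% to 2.5%. With the 4 physiological measures tested at a full 5%, and all tests independent, the chance over the 21 items is 21% to 47% in either direction and 11% to 27% in favour of telenursing.

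**Effect of adjustment.** Bonferroni across the list uses 0.05/21 = 0.0024 per test, and 1 − (1 − 0.05/21)^21 = 4.9%.

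**The case against.** The best case against the point has three parts.

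First, the hierarchy exists. SCN at T1 is named as the single primary outcome in several sections and the sample size rests on it. Section 3.1 labels the rest as secondary, down to "PROs at one, three and six months (secondary outcomes". This stands, and it is why the primary test is unaffected. But 2.7 does not carry the distinction into its significance rule.

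Second, this is a condensed article, and handling of multiplicity is often left to a statistical analysis plan. That would dispose of a complaint about a missing adjustment alone. Here, however, the article states an unqualified threshold and separately assigns the symptom comparisons an effectiveness purpose. The combination is in the text. The verb explore in 1.2 does not soften it: there it governs the comparison of professional-reported with patient-reported events, not the symptom list.

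Third, the size of the problem is easily overstated. A reader might infer that a false claim of benefit is more likely than not. The 21 items do not support that: 66% counts results in both directions, and the share favouring telenursing is 41% at most under independence, less with correlation or Fisher's test. Even with 35 tests, it falls below one half at a correlation of 0.2 (44%). A reader might also double the list to 42 tests, for incidence and severity, and reach 1 − 0.95^42 = 88%. That treats two strongly dependent measures of the same symptom as independent, and the article does not say that each item is tested twice.

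Nor do the documents define a success rule under which a significant secondary result would rescue a failed primary. Section 1.2 states an aim, not a decision rule, and section 3.2 calls for testing in larger samples.

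**Conclusion.** The point holds at a moderate size. As written, the plan applies one unadjusted threshold to 21 comparisons intended as evidence of effectiveness, and to at least 14 others. With no true effect, the 21 items carry up to about a 66% chance of at least one false significant difference, or about 41% in favour of telenursing. Under the illustrative assumptions on correlation and on Fisher's test, the latter figure drops to between 11% and 37%; with 35 independent tests it rises to about 59%.

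All these figures depend on the number of tests, their correlation and the test used, none of which the article fixes. Nearly all of them remain several times the 2.5% that applies to the primary test in that direction. The conclusion on SCN at T1 is untouched; what needs restraint is the language allowed for everything else.

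**What to change.** Add to section 2.7 that the comparison of SCN at T1 is the only confirmatory test, at two-sided 0.05. State that all other outcomes, including SCN at T2 and T3, will be reported as exploratory between-arm estimates with 95% confidence intervals and without declarations of significance. If the sponsor wishes to use the symptom and vital-sign list to support effectiveness, fix in advance which comparisons form that family and apply Holm or a false discovery rate procedure across it.

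The change takes two or three sentences and leaves the sample size and data collection as they are. The cost is that unadjusted significance claims on secondary outcomes are given up. Under Holm with 21 comparisons, the smallest p-value would have to be no larger than 0.05/21 = 0.0024, a demanding requirement with 20 patients per arm.
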